
### Aim 1. To examine short-term and longitudinal behavioral outcomes associated with the MFG

#### Hypothesis

Children who participate in MFG with their families will display significantly reduced conduct difficulties and increased functioning over time compared to those involved in the comparison condition. We expect that parent peers will evidence significantly more success engaging families to attend MFG sessions; thus, children in the MFG-parent-peer-delivered condition will evidence greater improvement relative to the other two study conditions.

We will consider a random-effects model for the child outcome variables across time as a function of treatment group, time and the interaction of group by time. A number of features will be common to all models. First, two levels of nesting will be explicitly modeled (caregiver and facilitator perspectives). At the third level of nesting, models may condition on a series of dummy codes capturing possible school-level effects. Second, the effect of primary interest is the test of the study condition (e.g., MFG-parent peer, MFG-community worker, comparison) by outcome trajectory (child behavioral symptoms and functioning) interaction. Third, time will be coded judiciously in accordance with a priori hypotheses about the time lags of effects of the experimental interventions. To adequately model hypothesized trajectories, higher-order polynomials can be estimated under different centering specifications, providing for multiple interpretations of the intercept and low-order trend components. Time contrasts can also be orthonormalized to reduce potential problems of multicollinearity in models specifying higher-order growth forms. Relevant trajectory variance components will also be evaluated to determine if there is variation (which would then be modeled as a function of both constant and time-varying covariates).

### Aim 2. To compare the uptake and implementation of MFGs by trained family peers and CHWs

#### Hypothesis

Given the level of training that CHWs receive prior to the study, they will evidence higher-fidelity initially, yet with training and ongoing supervision, we expect these differences to decrease over time.

To evaluate the fidelity, quality of implementation for MFGs implemented by family peers and CHWs, we will carry out a series of descriptive analyses and examine level of fidelity in four domains (described above). We will examine fidelity by year first to understand any change patterns over time, and then will combine analyses across years if no meaningful differences are found. Finally, see random-effects modeling to be used to examine differences by implementers over time.

### Aim 3. To elucidate multi-level factors that influence uptake, implementation, and youth outcomes

The overall analytic structure uses a three-level, multi-level SEM (MSEM) framework with family level variables at level 1, facilitator variables at level 2, and school variables at level 3. The analytic structure is complex, so we highlight our approach using Fig. 1 as our primary reference. We will employ mediation analysis with two-level MSEM models as explicated by Preacher, Zhang and Zyphur [119] and extended to three level models by Preacher [87]. We will use a combination of limited information estimation frameworks (focused on sub-portions of the full model) and full information estimation frameworks (focused on the entire three-level model) to strategically answer questions. At level 1, child outcomes are modeled as a function of the family predictors (see Fig. 1), taking into account the clustering at the higher levels of the model. The follow-up (6-month) measures of the mediators and the outcomes are included within the model in a classic SEM panel model with autoregressive effects, thereby linking the follow-up data to the immediate post-test data. This is an advantage of using MSEM over traditional multi-level modeling. Different centering strategies (e.g., grand mean vs. group mean) can be explored to garner various perspectives on the data. This feature of the model provides perspectives on the relative importance of paths in Fig. 1. To ascertain perspectives of the effects of school-level variables on facilitator variables, random intercept MSEM with the facilitator variables can be estimated as a function of the school variables that include dummy-coded treatment variables (MFG-parent peer vs. MFG-CHW) impacting the school mediators of readiness, leadership support and climate, which in turn, affect the facilitator-level intercepts. This modeling, or variants of it, address aim 3.

#### Integration of qualitative and quantitative analyses

We will use three different formats as described by Creswell et al. [120] for merging or converging the two datasets by bringing them together, connecting them by having one build upon the other; and embedding one dataset within the other so that one plays a supportive role for the other. Merging will occur through data triangulation in which results of quantitative and qualitative analyses are placed side by side to determine whether each provides the same answer to the same question (convergence). Results of our qualitative analyses will be connected to results from our quantitative analyses when we use the former to provide explanations for unanticipated findings produced by the latter (expansion). Finally, results of qualitative analysis can be embedded within the analysis of quantitative data by helping to provide context for outcomes (complementarity).

#### Data quality and management

The study will be overseen by local principal investigators. They will monitor the trial on a continuous basis and report to the Multiple Principal Investigators (MPIs) on a weekly basis via email, telephone or in person. Moreover, the study data will be reviewed by the National Institute of Mental Health Data and Safety Monitoring Board (DSMB) twice a year. The DSMB is established independent of the researchers involved in the study. The Board will oversee conduct of the study, particularly participant safety and data integrity. The Board has access to all the safety and data quality information collected and has the authority to stop the study if the Board believes the study is leading to unacceptable risks to participants. The study team will submit a data report to the DSMB twice yearly and upon request. The data report and other submissions to the DSMB will adhere to the established reporting format developed in consultation with National Institute of Mental Health (NIMH) collaborator(s). The report will include the major variables necessary for monitoring study participant safety, data integrity, and protocol fidelity, including study participants’ enrollment and retention. All the data reported to DSMB will be de-identified data to protect participants’ privacy. The DSMB will also review the study protocol, informed consent forms and procedures, and all relevant documents before the onset of the study, and will review and approve amendments to these documents.

The MPIs and Data Coordinating Unit (DCU) will prepare updates to the DSMB twice a year. In collaboration with DCU, the in-country data manager will organize data reports regarding preliminary process and outcome analyses (data collection at 8 weeks) and share with the MPIs. If preliminary analyses reveal harm (outcomes of child behavior are disproportionately negative), the results will be thoroughly reviewed by the MPIs and DSMB to assess whether stopping is warranted. However, no negative results have been identified in prior studies using the MFG intervention.

This study will be stopped prior to its completion if:The intervention is associated with adverse effects that call into question the safety of the interventionDifficulty in study participant recruitment or retention will adversely affect the ability to evaluate the study endpointsAny new information becomes available during the trial that necessitates stopping the trial; orOther situations occur that might warrant stopping the trial

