We estimate that a total of 30 schools will allow us to identify sufficient number of youth and nest them within trained program facilitators. This will allow the research team to detect a small to moderate effect based upon power calculations. Thirty schools is our best estimate of the total student population needed to draw a sufficient sample. The number of schools will be adjusted if needed.

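### The 8-week outcome analyses go to the principal investigators with no firewall, and their only stated route to the DSMB depends on a harm signal

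*Protocol article*

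**What the plan says.** All but one of the relevant statements stand in the protocol article under *Data quality and management*.

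- **Outcome analyses.** Working with the Data Coordinating Unit (DCU), "the in-country data manager will organize data reports regarding preliminary process and outcome analyses (data collection at 8 weeks) and share with the MPIs".
- **What follows from them.** "If preliminary analyses reveal harm (outcomes of child behavior are disproportionately negative), the results will be thoroughly reviewed by the MPIs and DSMB", to decide whether stopping is warranted. No threshold is given, and the sentence does not say who first decides that harm has been revealed.
- **Routine DSMB review.** "the study data will be reviewed by the National Institute of Mental Health Data and Safety Monitoring Board (DSMB) twice a year". Also, "The study team will submit a data report to the DSMB twice yearly and upon request".
- **DSMB powers.** "The Board has access to all the safety and data quality information collected and has the authority to stop the study". The board also approves amendments to the protocol.
- **Content of the DSMB report.** "The report will include the major variables necessary for monitoring study participant safety, data integrity, and protocol fidelity", with enrollment and retention named as part of this.
- **Who prepares it.** "The MPIs and Data Coordinating Unit (DCU) will prepare updates to the DSMB twice a year".

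The remaining statement is under *Randomization*, after the list of steps for selecting schools: "The number of schools will be adjusted if needed".

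**The concern.** The article sets out a procedure for interim outcome results, and the procedure runs in an unusual order. The people responsible for conducting the trial receive the outcome analyses. The independent board is brought in on those analyses once harm has shown itself.

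Two things are at stake.

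- **Freedom from bias.** The arms are visibly different (facilitated family groups against printed materials), and the main behaviour measures in Table 3 are reported by caregivers who know what their family received. If the MPIs and in-country staff also know how the arms are diverging at 8 weeks, that knowledge can colour training, contact with schools and data collection for families still in the trial.
- **Independence of the harm check.** Whether child-behaviour results are bad enough to raise an alarm is a judgement. With no threshold stated, it is better made by people with no stake in the result. As written, the board is not clearly the first reader, and the check is tied to one mid-course assessment.

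**Working it through.** The plan gives no threshold, alpha or information fraction for the 8-week check, so there is no figure to reproduce. The check is a comparison of statements.

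1. **Who receives the 8-week outcome analyses?** The sentence names the MPIs. It does not name the DSMB and states no restriction on what the MPIs may see.

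2. **What brings those analyses to the DSMB?** The next sentence does, and it opens with a condition: harm must be revealed. No other sentence mentions these analyses and the board together.

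3. **Does the routine report carry them anyway?** The listed content is safety, data integrity, protocol fidelity, enrollment and retention. Child-behaviour outcome analyses are not named. Study data are reviewed twice a year, so outcomes could be included, but the article does not say so. The MPIs and DCU prepare the board's updates. The 8-week reports might feed into them, but that too is unstated.

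4. **Are the analyses split by arm?** The text does not say. The harm criterion turns on outcomes being disproportionately poor, which needs a reference, and in a trial with a comparison arm the natural reference is that arm. A by-arm table is the natural reading, not a stated fact. No sentence limits the MPIs to pooled results.

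5. **Which assessments does the group-level harm check cover?** There are three after baseline: 8 weeks, 16 weeks and 6-month follow-up (10 months from baseline). Only the first is named, which is 1 of 3, taken halfway through a 16-week course (8/16). *Ethical considerations* does use the 8-week and 16-week data to track worsening, but as monitoring of individual participants by the research team. No group-level outcome review for harm is stated at 16 weeks or 6 months.

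6. **Are the recipients close to the conduct of the trial?** Yes. *Quality assurance plan* makes the MPIs and site PI responsible for recruitment, enrollment and data collection. *Ethical considerations* has the principal investigators directly involved in training research staff and facilitators. *Data collection* describes later delivery cycles with different families over 2 years, so 8-week results from early families could exist while later families are still being treated. The article does not show that this overlap will happen.

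7. **Is the open number of schools connected to these analyses?** Not in the text. *Randomization* ties the number to having enough students to draw the sample. It names no decision-maker, time point or data source.

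**The case against.** The strongest reply is that the DSMB is far from shut out. It reviews study data twice a year without any condition, receives reports on request, has access to all safety and data quality information, can stop the trial on its own judgement and approves amendments. The harm trigger may add a joint review on top of the routine one. This stands. A reader might infer that the board sees outcomes only if the investigators first decide there is harm, and the documents do not support that. What they support is narrower: the only *stated* route for these particular analyses is conditional. A right to ask for data does not put the 8-week results before the board as a matter of routine.

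A second reply is that this is a condensed article, and that closed reports and access rules usually sit in a DSMB charter. The article mentions a reporting format agreed with the funder. That would answer a complaint about silence. Here, however, the article names a recipient and a conditional sequence, and what is written can be corrected.

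Third, a reader might infer that the MPIs can enlarge the trial or vary supervision in response to interim outcomes, and might try to attach an inflated type I error to that. The documents do not support it. The school number is tied to student supply, with no decider named. The *Discussion* ties changes in outreach to recruitment, enrollment and retention. *Training and supervision* sets group supervision at 2 h per month. No interim information fraction or expansion rule is given from which an error rate could be worked out.

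Finally, later safety is not unwatched: the twice-yearly review and the adverse-effect stopping criterion have no 8-week limit. This also stands. The gap is confined to a stated group-level review of child-behaviour outcomes after 8 weeks.

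**Conclusion.** The concern holds in a limited form. The article sends preliminary 8-week outcome analyses to the investigators who run an open trial, states no firewall, and gives those analyses a route to the DSMB that depends on a harm signal with no threshold. The routine DSMB report does not name child-behaviour outcome analyses, and no group-level harm review of them is stated for 16 weeks or 6 months.

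This should be changed, but it is not a fatal flaw, given the board's independent powers. Its effect cannot be put as a number from these documents. The bias argument rests on two assumptions: that the reports show results by arm, which the harm wording implies but does not state, and that some families are still in treatment or assessment when the reports are read, which the repeated delivery cycles make possible. The argument for an independent harm check also supposes by-arm results, but it does not need the overlap in time.

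**What to change.** Change *Data quality and management* to say four things:

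- A DCU analyst sends by-arm child-behaviour tables directly to the DSMB in its existing twice-yearly report, beginning with the 8-week data and adding the 16-week and 6-month data as they accrue.
- The DSMB, not the MPIs, judges whether these tables signal harm.
- Arm comparisons are closed to the MPIs and the in-country team.
- The MPIs and in-country team receive pooled data and individual safety events only.

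As a minor clarification, *Randomization* can add that any change in the number of schools uses pooled recruitment and retention figures only. This matches the reason already given there.

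The cost is protocol and charter wording and a different recipient for the 8-week tables, with the later tables added to a report that already exists. The small downside is that the MPIs lose early sight of arm results. With two reports a year, an 8-week table could wait up to about 6 months (12/2) for the next scheduled one. The existing provision for reports on request lets the board ask for it sooner.

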#### Data Coordinating Unit (DCU)

This unit will be housed at Washington University in St. Louis and will be dedicated to the proposed research study. Data Coordinating Unit responsibilities include: (1) Creating a shared infrastructure that will facilitate the development and implementation of high quality study design, data collection, analysis, and development of publications across multiple projects (e.g., creation of a participant-tracking data base for scale-up study and small-scale implementation trials; assistance in creating data bases to organize data; assistance in planning and carrying out data entry and analyses of pilot data); (2) Developing core assessment battery data system (e.g., organize existing instruments; facilitate review of measures by collaborators to provide feedback); (3) Organizing consultation with on issues regarding protocol design, research methodology, measurement instruments and models, and data-analysis considerations.

#### Quality assurance plan

The MPIs and site PI are responsible at all phases of project implementation and for ensuring that the validity and integrity of the data, including study participants’ recruitment, enrollment, enrollment targets, and data collection procedures. MPIs, in collaboration with the site PI will implement quality assurance measures, including ongoing monitoring of the scale-up and pilot study activities, weekly correspondence with the local PI, and the timely reporting of any unexpected or expected adverse events that might occur during the study period. Moreover, the study will be monitored by external monitors twice a year (independent from investigators and the sponsor). The external monitors will write a report upon completing their audit, which will be shared with the local PI, MPIs, and the sponsoring institution (NIMH).

### Ethical considerations

This study poses more than minimal risk, but also has potential direct benefit for study participants. There may be psychological or privacy risks. Though highly unlikely, there is some risk for those in MFG groups of physically aggressive behavior because the study involves grouping children with behavioral challenges together:It is unlikely, though possible, that intervention facilitators may feel coerced into participating. We will assure all potential study participants that their participation is voluntary. Voluntary participation will be discussed with all potential participants and they will be instructed that if they choose not to participate, it will not affect their employment statusA second risk is the potential loss of confidentiality. Respondents may reveal sensitive information during family groups and/or data collection. All participating groups will be encouraged to respect and protect the confidentiality of information shared during groups. All research staff and facilitators will sign confidentiality pledges. If the research team detects breach of confidentiality by research staff or facilitator, their responsibilities related to the study will be terminated.We will also take the utmost caution to protect the confidentiality of responses to measures. Hard copies of documents and audiotapes will be maintained in locked file cabinets of a locked office in a secure building at the International Center for Child Health and Asset Development (ICHAD) in Uganda, at the School of Public Health at University of Ghana in Ghana, and at the Department of Psychiatry at University of Nairobi in Kenya. All data will be coded with ID numbers and stored in computerized datasets. All documents and audiotapes will be transported in locked carrier bags. Participant consent forms and ID logs will be kept in two separate locked cabinets in a separate in-country location. Tracking information also will be kept on a password-protected computer. The master list will only be used to coordinate data collection and all staff will be required to receive training on both study participants protections, as well as maintaining the confidentiality of participantsFor those in MFG groups, though highly unlikely, there may be some risk of physically challenging behavior because the program involves having children with behavioral challenges in a group setting together. The PI has conducted research studies using this intervention for over a decade and never experienced a physically aggressive incident. However, to minimize risk, both research staff and facilitators will be trained to diffuse these circumstances if they occur. The research team will make appropriate referrals to the families who need additional supportAmong families, the most serious risk in the proposed research is any adverse outcome that may jeopardize the welfare of a participating child or family. In general, when conducting child mental health service research with children and their families, potential risks of adverse outcomes exist as a consequence of the progression of a serious mental health issue or response to a service provided. The principle investigators will be directly involved in training all research staff (including senior project coordinator, research coordinator(s), and research assistants) and facilitators to identify key indicators of any increase in physical or mental health problems among the children and families participating in the studies across the three countries. In addition to facilitators’ observations in each session, the study participants will be monitored throughout the study and data on targeted outcomes will be collected at the mid-point of the intervention as well as at 16 weeks, the end of the intervention. That will give the research team the opportunity to track potential worsening of symptoms. Research staff will be on site at least every other session, which will give facilitators the opportunity to communicate any observation of worsening symptoms. All reporting will be documented

In addition to weekly meetings with children and their caregivers, as part of the intervention over the course of 16 weeks, the research team will monitor individual study participants throughout the study and data on targeted outcomes will be collected at the mid-point of the intervention as well as at 16 weeks, the end of the intervention. That will give the research team the opportunity to track potential worsening of symptoms. There is a potential risk that a child participant’s symptoms may worsen as a consequence of the progression of a serious mental health issue or in response to a service provided. If this occurs, the participant’s study participation will be halted and the in-country research team will make the necessary referrals in coordination with the local PI. Moreover, significant impairment/deterioration will be assessed via observation (e.g., physical presentation during the study), and/or caregiver/child self-report (e.g., disclosure of suicidal ideation)5.Participants may feel discomfort in answering some questions in the measures. They will be reminded during data collection, that they can skip any questions that they do not feel comfortable answering

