## Methods

The proposed study will be conducted across primary schools representing both semi-urban and rural communities. We expect to involve 3000 youths (in primary schools grades 2 through 7; 8 to 13 years) and their adult caregivers (3000) in Uganda. Schools will be randomly assigned to three study conditions: (1) MFG delivered by trained family peers; (2) MFG delivered by CHWs; or, (3) comparison: mental health materials. Data will be collected at baseline, 8 and 16 weeks, and 6-month follow-up (10 months from baseline; see Fig. 2 for the Standard Protocol Items: Recommendations for Interventional Trials (SPIRIT) schedule of enrollment, interventions, and assessments). A SPIRIT checklist (see Additional file 1) has also been included for further details on the study protocol.

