#### Description of the comparison condition

Mental health wellness materials from the MOH will be made available to all children and families recruited in the study (across all the three study conditions). We will adapt printed materials on child mental health based on those recently created by the MOH.

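### The rule that halts study participation when symptoms worsen does not say that outcome assessment continues, and worsening can be noticed through an extra route in the MFG arms, so the comparison could tilt toward MFG

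*Protocol article*

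**What the plan says.** Ethical considerations recognises that a child's "symptoms may worsen as a consequence of the progression of a serious mental health issue or in response to a service provided". If that happens, the child's "study participation will be halted and the in-country research team will make the necessary referrals". The rule covers every arm. It is not limited to the intervention, and nothing in the article says what becomes of the outcome visits still due.

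The same section describes how worsening is to be noticed:

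- **All arms.** "the research team will monitor individual study participants throughout the study and data on targeted outcomes will be collected at the mid-point" of the intervention and again at 16 weeks.
- **MFG arms only.** Facilitators observe in each session, and "Research staff will be on site at least every other session, which will give facilitators the opportunity to communicate any observation of worsening symptoms". The weekly meetings belong to the intervention: "In addition to weekly meetings with children and their caregivers, as part of the intervention over the course of 16 weeks".

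The comparison condition consists of materials, without sessions or facilitators: "Mental health wellness materials from the MOH will be made available to all children and families recruited in the study".

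On assessment times, Methods says: "Data will be collected at baseline, 8 and 16 weeks, and 6-month follow-up". Aim 1 tests the condition-by-trajectory interaction for child behavioural symptoms and functioning, using random-effects models over the four assessments. Sample attrition and retention adds a check for attrition bias from data collected before dropout, with hot deck imputation where possible.

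**The concern.** Two features act together. First, the event that ends participation is close to the primary outcome, so whether a later score is missing depends on what that score would have been. Second, one way of noticing the event exists only in the MFG arms. If poorly faring children leave the data sooner or more often under MFG, the MFG children still being measured look better than the arm as a whole.

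The planned methods do not clearly repair this. Random-effects models keep the scores recorded before a halt, and hot deck imputation borrows from pre-dropout data. Worsening seen in a session between two scheduled assessments, and acted on before the next one, never reaches an outcome scale, so neither method can use it.

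Safety review is also touched. Data quality and management has preliminary 8-week outcome analyses examined for harm to child behaviour. Children halted before week 8 could be absent from that comparison.

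**Working it through.** The article states no figure for this mechanism, so there is nothing to reproduce. The checks below show direction and range only. Every trigger and halting rate is an assumption.

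**Inputs from the article:** 1000 dyads per arm (Abstract); detectable effects of 0.10 SD (family) and 0.39 SD (school) at 80% power (Table 1); attrition of at most 20% by the end of follow-up (Sample attrition and retention).

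**Check 1: closed form, no true effect, means of those still observed.** Let the change score be N(0,1), with higher meaning worse. A fraction q of children, the worst, meet the trigger at cut-off c = z(1−q). In a given arm a share h of them is halted and lost. The mean of those remaining is

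−h·φ(c) / (1 − q·h)

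and the bias is the MFG value minus the comparison value. For q = 0.10, c = 1.2816 and φ(c) = 0.1755. With h = 0.8 under MFG and 0.3 in comparison:

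- MFG: −0.8 × 0.1755 / 0.92 = −0.153
- Comparison: −0.3 × 0.1755 / 0.97 = −0.054
- Difference: about 0.098 SD in favour of MFG

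All scenarios (SD in favour of MFG):

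| Share triggering, q | 50% vs 25% halted | 50% vs 10% | 80% vs 30% |
|---|---|---|---|
| 1% | 0.007 | 0.011 | 0.013 |
| 5% | 0.027 | 0.043 | 0.054 |
| 10% | 0.047 | 0.075 | 0.098 |

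With equal h in both arms the bias is 0. In children per 1000, the largest cell means 0.10 × 0.8 × 1000 = 80 halts in an MFG arm against 30 in comparison. The smallest means 5 against 2.5.

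**Check 2: does a likelihood analysis remove it?** Simulation with no true effect: 100,000 per arm, four visits, random-intercept variance 0.5, residual SD 0.5, and a persistent change of SD 0.5 arising in weeks 0 to 8. The worst 2%, 5% or 10% of changes trigger the rule. Halted children lose T2 to T4. Detection before T2 is 80% under MFG and 20% or 0% in comparison. The table gives the maximum-likelihood estimate at T4 under missing-at-random minus the complete-data difference in the same simulated sample. Negative values favour MFG.

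| Triggering | Comparison detection | Missed children stay in | Missed children halted at the 8-week visit |
|---|---|---|---|
| 2% | 20% | −0.024 − (−0.009) = −0.015 | −0.017 − (−0.009) = −0.008 |
| 2% | 0% | −0.023 − (−0.004) = −0.019 | −0.015 − (−0.004) = −0.011 |
| 5% | 20% | −0.042 − (−0.009) = −0.033 | −0.028 − (−0.009) = −0.019 |
| 5% | 0% | −0.044 − (−0.001) = −0.043 | −0.027 − (−0.001) = −0.026 |
| 10% | 20% | −0.058 − 0.001 = −0.059 | −0.033 − 0.001 = −0.034 |
| 10% | 0% | −0.079 − (−0.003) = −0.076 | −0.047 − (−0.003) = −0.044 |

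Where missed children stay in, observed T4 means give almost the same figures, so the likelihood analysis removes very little. Where they are all halted at week 8, the bias in observed T4 means falls to about 0, but the likelihood analysis still leaves about 0.01 to 0.04 SD. That is because comparison children leave with a T2 score and most of the halted MFG children leave without one. With detection certain in both arms the bias is about 0.

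**The case against.** The strongest reply is that the article never says outcome visits stop. Study participation may have been meant as the intervention only, and a condensed article may leave follow-up after a halt to the full protocol. That possibility stands. However, the halting rule is stated, not omitted. Under Inclusion/exclusion criteria the same term is used for the study as a whole, and that section elsewhere names research and intervention activities separately. As written, the literal reading is the natural one.

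Several limits also stand:

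- **Contact in the comparison arm.** A reader might infer that these children are seen only at scheduled assessments. The article does not support this, because it promises monitoring of individual participants throughout, without restriction by arm. The asymmetry is one additional route.
- **Contact under MFG.** Families are expected to attend at least seven or eight meetings, about half of the 16 weekly ones, so the gap in detection is smaller than weekly contact suggests.
- **Frequency.** The examples given with the rule, such as disclosure of suicidal ideation, point to marked deterioration, which may be rare. The article reports total attrition of 2.4% at 10 months in an earlier study by the team and says prior MFG studies identified no negative results.
- **Harm data.** A reader might infer that evidence of harm would be lost. That goes too far. Reports of worsening are to be documented, adverse events reported promptly, and safety and retention data sent to the DSMB twice a year. What could be depleted is the 8-week comparison of outcome scores.

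**Conclusion.** The point holds as a risk created by the wording. If the rule is applied literally, later outcome scores are lost for children whose symptoms worsen. Because the MFG arms have an extra way of noticing worsening, the likely direction of bias is toward MFG. The size cannot be determined from the article: about 0.01 SD if 1% of children trigger the rule, and up to about 0.05 to 0.10 SD if 5 to 10% do and the detection gap is large. The upper end is comparable with the 0.10 SD family-level detectable effect. Even that end is only about a quarter of the 0.39 SD school-level figure (0.10 / 0.39 = 0.26), and schools are the randomised unit.

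These sizes assume no true effect, persistent worsening and complete loss of scores after a halt. A reader might infer that the trial would show a benefit where none exists. The documents do not support that, because it would need halting rates that they do not give. The point deserves correction because the wording can be settled cheaply, and complete assessment after halting removes this source of bias.

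**What to change.** Leave the clinical halting and referral rule to the investigators. Reconcile the statement in Ethical considerations with the four-assessment analysis by adding, for data collection only:

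- Scheduled outcome assessments, at least those reported by the caregiver, continue after a halt unless consent or assent is withdrawn or the local PI judges assessment unsuitable for the child.
- The child is analysed in the arm to which the school was randomised.
- The date of each halt and the source of detection (session observation, scheduled assessment, caregiver or child report) are recorded and reported by arm, including to the DSMB alongside the 8-week outcome comparison.

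If the full protocol already provides for this, one clarifying sentence is enough. The cost is a small amendment, with the usual board approvals, and a few interviews already in the schedule. The records by arm would also show how often halting occurred, which would replace the assumed rates used above.
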